## Abstract

**Background:**

Many children and adolescents with psychiatric disorders struggle with sleep problems that oftentimes stay unaddressed in therapeutic settings due to limited resources. Still, there is evidence that improving insufficient sleep positively affects mental health recovery. Addressing an adequate sleep hygiene is named to be the first line of treatment when it comes to unspecific sleep problems. The present study aims to evaluate the efficacy of a brief sleep hygiene group intervention for children and adolescents with psychiatric disorders named “Ready for Landing.” The intervention is designed to improve sleep quality and elongate sleep duration by explaining the process of falling asleep using the metaphor of an airplane landing. Elements of psychoeducation and cognitive behavioral therapy for insomnia are combined.

**Method:**

The study plans to investigate the efficacy of the intervention using a waitlist control design. A sample of children and adolescents (aged 10–18 years) that are undergoing treatment for psychiatric disorders in day treatment centers in Kiel and Rostock, Germany, will be included. Sleep quality is assessed using the Pittsburgh Sleep Quality Index. Sleep duration is assessed by using a sleep diary completed by the patients and as well using actigraphy as an objective measure. Analysis of variance will be used to detect treatment effects. Secondary outcomes include variables regarding sleepiness.

**Discussion:**

If “Ready for Landing” proves to be efficacious the intervention has the potential to bridge the gap between frequent sleep problems in youth with mental health problems and limited resources to target those. Serving as an effective and economic tool, it could support mental healthcare professionals. It is a promising intervention to support the positive outcome of mental health treatments by improving sleep in children and adolescents.

**Clinical trial registration:**

https://www.bfarm.de/DE/Das-BfArM/Aufgaben/Deutsches-Register-Klinischer-Studien/_node.html, identifier DRKS00034984.

## Introduction

1

Sleep disturbances and dissatisfactory sleep are highly prevalent in individuals with mental health problems. For example, in children with autism spectrum disorder, a prevalence for sleep problems ranging from 60 to 86% is reported (Souders et al., 2017). In ADHD, an estimated 25–50% of patients suffer from sleep disturbances (Al Lihabi, 2023) while other studies report prevalence rates up to 70% (Martin et al., 2020; Loram et al., 2023). Regarding mood disorders, Asarnow and Mirchandaney (2021) reported that among adolescents with major depression, the prevalence of sleep disturbances ranges from 33 to 72.7%, depending on age and the specific definition used. For children and adolescents suffering from bipolar disorder, estimates range from 21 to 82%. In children and adolescents with anxiety disorders, parents of 85% of the participants reported sleep disturbances, while 52% of the youth themselves indicated trouble sleeping. Given the variety of disorders with cooccurring sleep difficulties those are mostly considered unspecific, transdiagnostic symptoms and are sometimes regarded as secondary due to their high prevalence (Freeman et al., 2020). This is concerning, as sleep disturbances might be a risk factor for the development (Reynolds and Alfano, 2016) and maintenance (Baglioni et al., 2011; Baglioni et al., 2016; Inada et al., 2021) of psychiatric disorders and detrimental (Inada et al., 2021) to the effect of therapeutic interventions.

The sleep of children and adolescents undergoes significant changes during puberty, which can further increase the risk to develop sleep disorders and may contribute to the onset or worsening of other psychiatric disorders (Tarokh et al., 2014; Reynolds and Alfano, 2016). For children and adolescents who are already affected by mental health conditions, research indicates rising strain from sleep problems in parallel to the severity of those mental health concerns (Boafo et al., 2021). Accordingly, improvement in sleep hygiene can be seen as a first line treatment or prevention to reduce the impact insufficient sleep has on those with mental disorders. It has proven effective in the treatment of various mental health conditions (Freeman et al., 2020; Tarokh et al., 2014; Gupta et al., 2019; van der Heijden et al., 2018; Boafo et al., 2021; Inada et al., 2021; Hertenstein et al., 2022). In adults treatment guidelines recommend sleep hygiene as part of Cognitive Behavioral Therapy for Insomnia (CBT-I) as first line and gold standard treatment (Hertenstein et al., 2022). Sleep hygiene mostly incorporates behavioral modification and lifestyle based interventions that improve both sleep quality and quantity and promote better sleep (Baranwal et al., 2023). The need for accessible and effective interventions targeting sleep and sleep hygiene is further highlighted in a study by Quon et al. (2018) which found that nearly one-third of children and 71% of adolescents visiting a mental health outpatient center had poor sleep quality. The results furthermore indicated, that when focusing on specific domains of insufficient sleep quality, 88% of the children and 97% of the adolescents showed a problem in at least one of the seven domains assessed by the Pittsburgh Sleep Quality Index (PSQI; Buysse et al., 1989). The need for those interventions has led to the development of a variety of interventions, as for example F.E.R.R.E.T (Tan et al., 2012), which targets different domains of behavioral and cognitive modification strategies and is suitable for various patient-and age groups, or TransC-Youth (Harvey et al., 2025), which was evaluated for the use in an individual and group therapy community setting. So far, there is a high variety of interventions, which need to be further developed but also critically evaluated with high-quality evaluative studies (McLay et al., 2024; Hall and Nethery, 2019; Chung et al., 2018; Nikles et al., 2020). It hast to be noted that stand-alone sleep hygiene interventions, when not implemented as part of CBT-I, are not the recommended gold-standard treatment for diagnosed insomnia (Deutsche Gesellschaft für Kinder-und Jugendpsychiatrie, Psychosomatik und Psychotherapie e.V. (DGKJP), 2018). However, they are recommended as a first line treatment for children and adolescents with psychiatric disorders that present with comorbid sleep disturbances (van der Heijden et al., 2018; Tarokh et al., 2014). To account for highly prevalent sleep problems and to address the need for easily implementable interventions we developed a group intervention focused on sleep hygiene that includes psychoeducation as well as some few easy-to-learn elements of cognitive behavioral therapy for insomnia. Since most of the participants have not been diagnosed with insomnia, but suffer from sleep problems nevertheless, the intervention addresses their need for improved sleep. The group intervention uses a metaphorical framework, linking the principles of sleep hygiene to pictorial language to help children and adolescents memorize the rules.

In this context, the intervention “Ready for Landing” (RfL) presented in this protocol explains the principles of sleep hygiene by using a metaphor of a landing passenger plane. It uses psychoeducation as well as elements based in CBT-I, such as problem-solving strategies and strategies to overcome barriers in establishing new behaviors (Schlarb, 2015). This aims to convey knowledge while also empowering participants with tools to use it. We intentionally do not incorporate elements such as bedtime restriction. Despite being highly efficacious, these require closer supervision and elongated time for treatment than what is feasible in brief group-therapy sessions or during patient one-on-one therapeutic contacts focusing on primary mental health concerns. We strongly believe the presented combination of psychoeducation with CBT-I strategies therefor offers an accessible, time-efficient way to address common co-occurring sleep problems in mental conditions that led to the admission. Further implemented elements include explanations regarding the functionality of sleep and the development of behavioral intentions and coping mechanisms to overcome potential obstacles when implementing new sleep hygiene routines. Those techniques have been shown to improve sleep quality, sleep hygiene and overall wellbeing, for example, by restructuring or limiting negative thought processes concerning sleep, applying stimulus control or working with sleep related beliefs and the theory of planned behavior (Lin et al., 2018; Meltzer and Mindell, 2014; Chung et al., 2018).

### Aim of the study and hypotheses

1.1

The present study aims to evaluate the efficacy of a group therapy-based sleep hygiene intervention within day clinic treatment for children and adolescents with psychiatric disorders. We expect to improve sleep quality and elongate sleep duration in children and adolescents with mental health problems by implementing “Ready for Landing” (RfL). On an exploratory level we aim to investigate the intervention’s effect on the sleep onset latency and sleepiness. An additional aim of this study is to investigate the circadian rhythm with regard to its stability and variability, as well as the relationship between subjective (sleep diary and questionnaires) and objective data (actigraphy) on sleep quantity and quality. For this aim an additional study protocol will follow.

## Methods and analysis

2

### Study design

2.1

The study is conducted using a waitlist-control-design. Each participant attends three sessions in a group therapy setting, with session T0 and T1 forming the primary focus to detect a treatment effect (Figure 1). The third timepoint, T2, serves for further exploratory analysis and to deliver the intervention to the control group as well. Two out of three sessions are the RfL-sessions, while a third one is of an unrelated topic. Participants are quasi-randomized into intervention or control group. Allocation of participants to the group is based on the time they begin treatment in the facility. Whether the participants belong to the control or intervention group is determined by the alternating nature of their occurrence. After an intervention group lasting 28 days an about 8–10 weeks pause interval follows to reach a sufficient amount of new, naive-to-the treatment admissions. After that a control group of 28 days starts, also followed by an 8–10 weeks pause interval afterwards. This process, alternating between intervention and control group with an 8–10 weeks pause interval in between, is continued until the required number of participants has been reached. Participation from start to end lasts 28 days representing 4 weeks around the described timepoints. The measurements collected for this study consist of different self-report questionnaires, sleep logs and actigraphy data. Psychometric properties of the questionnaires used are described below.

**Figure 1 fig1:**
[figure not shown]
Study design “Ready for Landing” (RfL). Participation consists of 3 sessions in both conditions. The intervention group starts with the two RfL sessions and finishes with intervention-unrelated group therapy while the control group starts with the intervention-unrelated group therapy and then receives the RfL intervention. Intervention and control group are conducted in consecutive, alternating turns separated by an 8–10 weeks pause interval.

#### “Ready for Landing”—the intervention

2.1.1

“Ready for Landing” (RfL) is conceptualized as a brief, group therapy-based intervention that teaches the principles of sleep hygiene through the metaphor of a passenger plane landing. The intervention is administered by mental health professionals, including psychotherapists, psychologists and social workers. The intervention follows a manual and is therefore standardized in its implementation. All mental health professionals involved receive training on the regimen of the study and the manual of the intervention to ensure quality standards are met.

The intervention consists of two 90-min sessions held 1 week apart from each other. In the intervention group those sessions take place at T0 and T1, the control group undergoes the intervention at T1 and T2. To give patients as much control as possible over their sleep routine, the intervention is implemented in day-clinic treatment settings for children and adolescents in psychiatric care. During the first session, patients learn about the functionality of healthy sleep, reflect on their own current sleep quality, sleep habits, and sleep hygiene and are introduced to the airplane metaphor. The metaphor explains sleep hygiene as a well-structured and segmented process consisting of different phases which enable pilots to land the plane safely, in other words to establish a good routine to go to sleep and is depicted in Figure 2. The landing of a passenger airplane is described to pass through 12 stages which are grouped into four phases: flight schedule, descent, landing approach and park position. In the “flight schedule” phase, consistent times for departure, as well as preparations regarding the takeoff and the flight itself are outlined. During “descent” service of food and beverages is stopped and passengers must remain seated. The patients are further advised not to take naps 3 h before bedtime. According to the common sleep hygiene recommendations it is emphasized not to nap after 3 p.m. The difficulty, however, was that the day clinic treatment was not finished until around three o’clock. In order to address this important rule, therefore the time window had to be adjusted accordingly (no nap 3 h before bedtime). Although the time stated on the poster may seem too late, it was pointed out during training that it was important not to nap too late and certainly not 3 h before bedtime.” During the third phase, the “landing approach,” electronic devices have to be turned off (“flight mode”), passengers are told to sit back and relax and in case of turbulences or obstructions on the runway a loop is flown and landing is restarted shortly after. The fourth phase mainly targets the processes occurring when the plane landed and is pulled into its hangar. It is therefore named “Take park position” and describes the importance of a clean and functional but also welcoming hangar which is used for this purpose only. Each phase corresponds to a specific time window. The first phase mainly describes the day starting with getting up and ending with the time to start preparing for bedtime. The second phase, “descent,” covers 3 h before bedtime while the third phase, “landing approach,” comprises of the last 30 min before the planned bedtime. Phase four, “Take park position,” mainly consist of the night and daytime preparations making sure the sleeping place is ready when it needs to be.

**Figure 2 fig2:**
[figure not shown]
“Ready for Landing”-metaphor. Poster illustrating the airplane metaphor used for the intervention “Ready for Landing”: The poster is hung up between session 1 and 2 and used to explain the sleep hygiene rules during the sessions. The rules are also printed on cards that are used during the intervention.

After the introduction patients are told that mastering a smooth landing requires practice and it might also be helpful to practice one step at the time. They are encouraged to reflect their own current ability to “land” using a worksheet asking them about their current sleep hygiene. Afterwards they select one or two sleep hygiene rules at max to practice for the upcoming week. The group is guided to discuss possible obstacles and solutions targeting them to master the selected behavior. The second session consists of a free or cued recall of the 12 sleep hygiene rules depending on the group’s ability to memorize the rules in the beginning of the session. This is followed by a reflection of the patients’ “pilot training” over the last week. Patients are encouraged to continue working on their ability to land smoothly and are reminded that this process might take some time to be mastered. The participants are then awarded their pilot license when being able to correctly answer questions about the newly learned sleep hygiene rules in a quiz. At the end of the session patients can ask further questions about sleep and sleep hygiene and are awarded with a “flight tag” to thank them for their participation and to serve as a reminder for the newly learned principles.

#### Questionnaires and actigraphy

2.1.2

The study aims to detect improvement in subjective and objective domains of sleep following the intervention. Subjective sleep quality is assessed using PSQI (Buysse et al., 1989). The PSQI consists of 24 items covering seven domains of sleep quality including sleep quality, sleep latency, sleep duration, sleep efficiency, sleep disturbances, use of medication, and daytime sleepiness. The PSQI is a validated and widely used self-report measure for sleep quality showing good reliability, internal consistency, criterion validity and discriminatory power. A global score of five has been deemed sufficient to discriminate between good and bad sleep quality (Buysse et al., 1989). Those findings have been replicated for the use of the PSQI in minors (La Vega et al., 2015; Larche et al., 2021). To assess daytime sleepiness, we use the Epworth Sleepiness Scale for Children and Adolescents (ESS-CHAD, Janssen et al., 2017) which consists of eight items regarding the tendency to fall asleep during different age-adjusted daytime activities such as during lessons in school. The ESS-CHAD has been shown to be a reliable and valid measure to assess daytime sleepiness in minors (Janssen et al., 2017). Both questionnaires were chosen because they are applicable to our wide age range from 10 to 18 years of age likewise and are commonly used in sleep research. This ensures comparability within the group of participants and also allows to compare our results to those of other researchers. PSQI and ESS-CHAD are distributed at the beginning of every session so that the participants answer them before they receive any new elements of the intervention during the sessions. They are instructed to focus on symptoms present in the last week. Between sessions the patients keep a sleep log that monitors aspects such as bedtime, waketime, total sleep duration, duration until they fall asleep and subjective aspects such as perceived rest-and wakefulness each day during the week. Those subjective measures will be complemented by actigraph data to gain insides about possible incremental validity. The comparability of subjective and objective sleep data collected in this study will be subject of another study. Hence, this will be described in an additional study protocol, which aims to gain insight on subjective and objective measurements of sleep in youth with mental health problems.

In this study actigraphy will only be used in terms of assessing treatment effects on sleep duration (Total Sleep Time, TST). Therefor the MotionWatch 8 (Alpha Trace Ltd.) a wrist worn actigraphy watch worn continuously throughout the 28 day will be used. We will use MotionWatch Mode 1 and record 30 s epochs of movement and light information. Further analysis of actigraphy data such as sleep efficiency and the stability of sleep–wake-rhythm and all efforts to compare subjective and objective sleep data will be described in the additional protocol mentioned above.

At the end of the intervention participants provide feedback about perceived usefulness of the metaphor and materials, adherence during the intervention, intention to further adhere to the introduced behavior and further annotations, positive and negative. We further collect sociodemographic variables such as age, gender, living situation and completed and intended education, as well as current psychiatric disorders (ICD-10 diagnoses) and mental health problems. With this we intend to gain insight into the usefulness of the intervention across various psychiatric disorders and their respective symptom severity on an exploratory level.

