### Data analysis

2.9

The study is conducted using a control design in which the control group receives regular group therapy. To detect treatment effects, variance in between intervention and control group at T0 and T1 (see Figure 1) is assessed by using a repeated measures ANOVA including two factors (GROUP and TIMEPOINT). Significance level is set to be at *p* = 0.05. Post-hoc tests will clarify effect size and direction. If statistical assumptions are not met, non-parametric alternatives will be used. In additional exploratory analyses we plan to account for sociodemographic aspects or the influence of different diagnoses for the efficacy of the program.

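### For the PSQI, the primary T0–T1 contrast ends before the second session, so it estimates session 1 plus one week of practice and not the two-session programme on which the trial will draw conclusions

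*Protocol article*

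**What the plan says.** Section 2.1.1 defines the programme: "The intervention consists of two 90-min sessions held 1 week apart from each other". It then places the sessions by arm: "In the intervention group those sessions take place at T0 and T1, the control group undergoes the intervention at T1 and T2".

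Section 2.1.2 fixes when the questionnaires are filled in: "PSQI and ESS-CHAD are distributed at the beginning of every session so that the participants answer them before they receive any new elements". On the recall period it adds: "They are instructed to focus on symptoms present in the last week". Section 3.1 confirms the order for controls, who start RfL at T1 once the questionnaires are done.

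Section 2.1 describes the design "with session T0 and T1 forming the primary focus to detect a treatment effect", and section 2.9 matches it: "variance in between intervention and control group at T0 and T1 (see Figure 1) is assessed by using a repeated measures ANOVA". The last timepoint has a lesser role: "The third timepoint, T2, serves for further exploratory analysis and to deliver the intervention to the control group as well".

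Section 2.1.1 also describes the content. Session 1 covers how sleep works, the full metaphor with its 12 rules, self-assessment and planning for obstacles. On practice it says: "Afterwards they select one or two sleep hygiene rules at max to practice for the upcoming week". Session 2 is recall of the rules, reflection on the practice week, a quiz and questions.

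The aim (section 1.1) is the efficacy of the group intervention. The conclusion (section 4) describes that intervention as having two sessions.

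**The concern.** A primary contrast should compare the treatment named in the conclusion with its absence. Here the PSQI contrast closes before the intervention arm has received its second session.

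The risk is greatest for a null result. Section 3.1 asks whether two sessions are enough and suggests that a longer version may be needed. A null T0–T1 result would invite exactly that reading, although the test had measured one session and one week. A positive result would be evidence for RfL, but its size would belong to session 1 and not to the programme as delivered.

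**Working it through.** **Exposure at each questionnaire.** Counting RfL sessions completed before each PSQI (sections 2.1.1 and 2.1.2):

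| | T0 | T1 | T2 |
|---|---|---|---|
| Intervention arm | 0 | 1 | 2 |
| Control arm | 0 | 0 | 1 |
| Contrast | 0 v 0 | 1 v 0 | 2 v 1 |

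The primary test uses the first two columns. The contrast 2 v 0 appears nowhere. The ESS-CHAD, a secondary outcome, has the same timing.

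**Actigraphy sleep time.** Section 2.1.2 has the watch worn for 28 days but does not assign nights to T0 or T1. If T1 means the week before T1, the contrast is 1 v 0. If it means the week after, controls have had session 1 and the contrast is 2 v 1. Neither is 2 v 0.

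**The plan's sample size.** Section 2.4 gives effect size 0.25, power 0.90, alpha 5% and N = 46. For the within-between interaction with g = 2 groups and m = 2 timepoints:

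- λ = f² × N × m / (1 − ρ), with df1 = 1 and df2 = N − 2.
- The article gives neither ρ nor a sphericity correction. I assume ρ = 0.5 and sphericity.
- With f = 0.25 and N = 46: λ = 0.0625 × 46 × 2 / 0.5 = 11.5, and power is 0.912. At N = 44 power is 0.8997.

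N = 46 therefore reproduces with two timepoints. Three timepoints with the same ρ would give 36, so the figure fits a T0–T1 test. It reproduces when 0.25 is read as f; that the article labels it d is a separate matter.

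**Cost if part of the effect comes later.** Let the full two-session effect be f = 0.25 and let a share s be present at T1, so that λ = 11.5 × s². The documents do not give s, so a range is shown:

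| s (assumed) | λ at N = 46 | Power at N = 46 | N for 90% power |
|---|---|---|---|
| 1.00 | 11.5 | 0.91 | 46 |
| 0.90 | 9.3 | 0.85 | 54 |
| 0.75 | 6.5 | 0.70 | 78 |
| 0.50 | 2.9 | 0.38 | 172 |

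**What the collected data can identify.** Measure arm differences as change from T0. Let a be the effect of session 1 one week on, and b the effect at T2 of both sessions in the intervention arm.

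- T1 arm difference = a.
- T2 arm difference = b − a, if session 1 has the same one-week effect in both arms and the underlying time trends are equal.
- Sum = a + (b − a) = b, which is two sessions against none.

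**Precision of the sum.** Assume equal variance σ² and ρ = 0.5 between any two timepoints. Per participant:

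- Change scores: Var(Y1 − Y0) = 2(1 − ρ)σ² = σ², and Var(Y1 + Y2 − 2Y0) = (6 − 6ρ)σ² = 3σ². The standard-error ratio is √3 = 1.73.
- Baseline-adjusted: Var(Y1 | Y0) = (1 − ρ²)σ² = 0.75σ², and Var(Y1 + Y2 | Y0) = (2 + 2ρ − 4ρ²)σ² = 2σ². The ratio is √(2/0.75) = 1.63.

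The standard error is thus about 1.6 to 1.7 times that of the T1 contrast.

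**The case against.** The waitlist comparison at T1 is deliberate and openly stated. Section 3.1 explains that controls should benefit before they leave the clinic, names the missing follow-up and possible delayed effects, and questions whether two sessions suffice. The stated aim does not itself mention two sessions, and a positive T0–T1 effect would support RfL unless session 2 undid it. All of this stands. It lowers the weight of the point for a positive result, but section 3.1 still does not say that the primary contrast ends before session 2.

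Four stronger readings are tempting and are not supported.

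- A reader might infer that half the effect is missed, so that about four times the sample is needed. Half is only a count of sessions. Section 2.1.1 puts most of the new content in session 1, so the missed share may be well below half.
- A reader might infer that every primary outcome is measured before session 2. The article fixes that timing only for the questionnaires.
- A reader might infer that no two-session comparison is planned. T2 is assigned to exploratory analysis whose content is not described, and the full plan is not shown. What is established is that the primary contrast is not two against none and that this contrast is never directly observed.
- A reader might infer that the trial cannot answer its question at all. It answers a narrower one.

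**Conclusion.** The point holds. For the PSQI, the primary T0–T1 contrast estimates session 1 plus one week of practice against an unrelated session. This follows from the stated timing and needs no numerical assumption. For actigraphy sleep time, the contrast is either one against none or two against one, depending on nights that the article does not specify.

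The size of the consequence is uncertain. If 90% of a full effect of f = 0.25 is present at T1, power at N = 46 falls only from 0.91 to 0.85. At 75% it is 0.70 and at 50% it is 0.38. These figures rest on ρ = 0.5 and on shares that the documents do not give. The mismatch between the contrast and the conclusion remains at any share, and it matters most for how a null result is read.

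**What to change.** **(a) Align question, window and conclusion.** State the primary question and conclusions as the effect of session 1 plus one week of practice against an unrelated group session. Define the T1 actigraphy window as the nights between T0 and T1. Add to section 3.1 that the primary contrast precedes session 2, and state that a null result will not be read as failure of the two-session programme.

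**(b) Pre-specify one supportive analysis.** Fit a mixed model with arm-by-timepoint terms to T0, T1 and T2, and to the matching actigraphy weeks. Report the T1 arm difference plus the T2 arm difference, with a confidence interval, as the estimate of two sessions against none. State its assumptions: equal time trends, and the same one-week effect of session 1 in both arms.

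A zero arm difference after T2, when both arms have had two sessions, can serve as a check only under the added assumption that effects do not grow with elapsed time. The summed estimate itself does not need that assumption. The check also needs actigraphy nights after T2, which the article does not confirm; it describes no PSQI after T2.

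**Cost.** Wording changes, one window definition and one extra model; no new visits or data. The downside is precision: with a standard error about 1.6 to 1.7 times that of the T1 contrast (assumed ρ = 0.5), the two-session estimate should remain supportive.
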